### Measures

All outcome measures are locally validated and have been selected to capture the primary outcome, secondary outcomes and potential mechanisms of change. All outcome assessments will be conducted face-to-face at the participant’s preferred time and location across baseline (T0), as well as at 2 months (T1), 4 months (T2), and 6 months (T3) from baseline, and at 12 months (T4) and 24 months (T5) after the completion of the intervention. To minimize participant burden, outcome measures are prioritized and staggered across timepoints (see Table 2). All assessments will be administered by experienced, independent interviewers blinded to intervention allocation. All interviewers will undergo rigorous training involving comprehensive familiarization with the measurement tools, clinical vignettes, and on-site practice to achieve and maintain high inter-rater and intra-rater reliability (ICC >0.9) throughout the study.

#### Primary outcome

Loneliness will be assessed by the 20-item Revised UCLA Loneliness Scale (UCLA-LS) (59, 60), where participants will rate each item based on the frequency they experience feelings of loneliness, using a 4-point Likert scale ranging from 1 = Never to 4 = Always. Total scores range from 20 to 80, with higher scores indicating greater levels of loneliness.

#### Secondary outcomes

Loneliness will also be measured by the 6-item De Jong Gierveld Loneliness Scale (DJGL) (61, 62). Participants will rate their agreement with each statement on a 3-point Likert scale ranging from 1 = Yes to 0 = No. DJGL includes two subscales: emotional loneliness (3 items) and social loneliness (3 items). Total scores range from 0 to 6, with subscale score ranging from 0 to 3. A high score indicates higher levels of loneliness.

Sleep quality will be assessed by the 19-item Pittsburgh Sleep Quality Index (PSQI) (63, 64). PSQI evaluates seven components of sleep: sleep quality, sleep latency, sleep duration, sleep efficiency, sleep disturbance, use of sleep medication, and daytime dysfunction. Participants will rate each item on a 4-point Likert scale ranging from 0 = No difficulty to 3 = Severe difficulty. Total scores range from 0 to 21, with higher score indicating worse sleep quality.

Life satisfaction will be assessed by the Satisfaction with Life Scale (SWLS) (65, 66). Participants will rate their agreement with each statement related to subjective well-being and life satisfaction on a 7-point Likert scale ranging from 1 = Strongly disagree to 7 = Strongly agree. Total scores range from 5 to 35, with a higher score indicating greater life satisfaction.

Perceived stress will be assessed by the 14-item Perceived Stress Scale (PSS) (67, 68). Participants will rate the frequency with which they experienced each feeling in the past month on a 5-point Likert scale ranging from 0 = Never to 4 = Very Often. Some items will need to be reverse coded before summing. Total scores range from 0 to 56, with a higher score indicating more stress.

Mental health will be assessed by the 14-item Hospital Anxiety and Depression Scale (HADS) (69, 70). Participants will rate the intensity of each symptom on a 4-point Likert scale ranging from 0 = Not at all to 3 = Most of the time. HADS consists of two subscales: anxiety (7 items) and depression (7 items). Total scores range from 0 to 42, with subscale score ranging from 0 to 21. A higher score indicates greater severity of anxiety or depression.

Cognitive functioning will be assessed by the Montreal Cognitive Assessment (MoCA) (71, 72). MoCA consists of seven cognitive domains: executive functioning, naming, memory, attention, language, abstraction, and orientation. Participants will complete 11 tasks, and total scores range from 0 to 30, with a higher score indicating better cognitive performance.

Physical heath will be assessed in five ways: Barthel Index of Independence in Activities of Daily Living (ADL) (73), Lawton Instrumental Activities of Daily Living Scale (IADL) (74, 75), 18-item Physical Symptoms Inventory (PSI) (76, 77), Charlson Comorbidity Index (CCI) (78), and 6-Minute Walking Test (6MWT-CHN) (79, 80). For ADL, participants will rate their current level of ability across 10 items assessing activities of daily living on a scale of 0 = dependent to 5/10 = independent. Total scores range from 0 to 100, with higher scores indicating greater independence. For IADL, participants will rate their ability in performing 8 specific tasks on a scale of 0 = dependent to 1 = independent. Total scores range from 0 to 8, with higher scores indicating greater independence. For PSI, participants will rate the presence of each symptom in the past 30 days on a 5-point Likert scale ranging from 0 = Never to 4 = Often. Total scores range from 0 to 72, with a higher score indicating a greater number and frequency of reported symptoms. For CCI, participants will indicate the presence of a list of 16 comorbid conditions (e.g., heart failure, diabetes, chronic pulmonary disease, lymphoma). Each condition is assigned a weighted score based on its associated risk of mortality, leading to a total score ranging from 0 to 37. Higher scores indicate a greater burden of comorbidities and predict a higher risk of mortality. For 6MWT-CHN, participants will be asked to walk the furthest distance possible in 6 min; they may slow down, stop, and rest during the test, but should resume walking as soon as they are able. Before and immediately after the walking test, participants will rate their level of breathlessness using the Borg scale from 0 = No breathlessness to 10 = Maximal breathlessness. The total distance walked in 6 min will be recorded as well.

#### Mediators

Mindfulness will be assessed by the 15-item Mindfulness Attention Awareness Scale (MAAS) (81). Participants will rate the frequency of each experience on a 6-point Likert scale ranging from 1 = Almost always to 6 = Almost never. A mean score across all items will be calculated, with higher scores indicating higher levels of dispositional mindfulness.

Self-compassion will be assessed by the 12-item Self-Compassion Scale-Short Form (SCS-SF) (82, 83). SCS-SF comprises six subscales: self-kindness, self-judgment, humanity, isolation, mindfulness, and over-identification. Participants will rate how often they behave in the manner described by each statement on a 5-point Likert scale ranging from 1 = Almost never to 5 = Almost always. A mean will be calculated for each subscale and overall scale, with higher scores indicating higher levels of self-compassion.

Thought patterns will be assessed by the Emotion Regulation Questionnaire-Cognitive Reappraisal subscale (ERQ-CR) (84, 85). Participants will rate the extent to which they engage in cognitive reappraisal through their speech, gesture, or behavior on a 7-point Likert scale ranging from 1 = Strongly disagree to 7 = Strongly agree. A mean score will be calculated, with higher scores indicating greater use of cognitive reappraisal as an emotion regulation strategy.

Social support will be assessed by the 12-item Multidimensional Scale of Perceived Social Support (MSPSS) (86, 87). Participants will rate their perceived support from three: family, friends, and significant others on a 7-point Likert scale ranging from 1 = Strongly disagree to 7 = Strongly agree. Total scores range from 12 to 84, with subscale score ranging from 4 to 28. A higher score indicates higher levels of perceived support.

Social network will be assessed by the 6-item Lubben Social Network Scale (LSNS-6) (88, 89). Participants will rate how many family members and friends they can engage with in terms of frequency of contact, closeness for discussing private matters, and availability for help on a 6-point Likert scale ranging from 0 = None to 5 = 9 or more. Total scores range from 0 to 30, with a higher score indicating greater social engagement and lower risk of social isolation.

Neighbourhood collective efficacy and identity will be assessed by the modified 8-item Neighbourhood Collective Efficacy Scale (NCE) (90, 91). Participants will rate statements focusing on social cohesion and informal social control in their neighbourhood on a 5-point Likert scale ranging from 1 = Strongly agree to 5 = Strongly disagree. A mean score will be calculated, with higher scores indicating greater social control, cohesion, and trust.

#### Cost-effectiveness

Quality of life will be assessed by the EuroQol 5-Dimension 5-Level Instrument (EQ-5D-5L) (92, 93). EQ-5D-5L consists of two parts: descriptive system (EQ-5D) and a Visual Analogue Scale (EQ-VAS). In the descriptive system, participants will rate their health status across five dimensions: mobility, self-care, usual activities, pain/discomfort, and anxiety/depression on a 5-point Likert scale ranging from 0 = No problem to 5 = Unable to perform. For the EQ-VAS, participants will rate their overall health status on the day of assessment from 0 = Worst health to 100 = Best health.

Healthcare service usage will be evaluated using a self-designed scale. Participants will report the frequency of their use of outpatient medical treatment, accident and emergency treatment, and inpatient medical treatment over the past 3 months at both public and private facilities. Frequencies will be rated on a scale from 0 = none to 3 = three times or more.

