**Figure 2 fig2:**
[figure not shown]
CONSORT flow diagram.

**Table 1 tab1:** Schedule of enrolment, interventions, and assessments for SPIRIT 2025.

	Study period						
	Enrolment		Post-randomization				Close-out
Timepoint	−*t*_1_	*t* _0_	*t* _1_	*t* _2_	*t* _3_	*t* _4_	*t* _5_
Enrolment							
Eligibility screen	×						
Informed consent	×						
Randomization		×					
Interventions							
First-arm (individual-level only)			×				
Second-arm (individual- + interpersonal-level)			×	×			
Third-arm (individual- + interpersonal- + community-level)			×	×	×		
Fourth-arm (education-only control group)			×	×	×		
Maintenance				×	×		
Assessments							
Primary outcomes							
Revised UCLA Loneliness Scale (59, 60)		×	×	×	×	×	×
Secondary outcomes							
De Jong Gierveld 6-item Loneliness Scale (61, 62)		×	×	×	×	×	×
Pittsburgh Sleep Quality Index (63, 64)		×	×	×	×	×	×
Satisfaction with Life Scale (65, 66)		×	×	×	×	×	×
Activities of daily living (73)		×				×	×
Instructional activities of daily living (74, 75)		×				×	×
Physical Symptoms Inventory (76, 77)		×	×	×	×	×	×
Charlson Comorbidity Index (78)		×				×	×
6-Minute Walking Test (79, 80)		×				×	×
Perceived Stress Scale (67, 68)		×	×	×	×	×	×
Hospital Anxiety and Depression Scale (69, 70)		×	×	×	×	×	×
Hong Kong Montreal Cognitive Assessment (71, 72)		×				×	×
Mediators							
Mindfulness Attention Awareness Scale (81)		×	×	×	×	×	×
Self-Compassion Scale-Short Form (82, 83)		×	×	×	×	×	×
Emotion Regulation Scale-Cognitive Reappraisal subscale (84, 85)		×	×	×	×	×	×
Multidimensional Scale of Perceived Social Support (86, 87)		×	×	×	×	×	×
Lubben Social Network Scale (88, 89)		×	×	×	×	×	×
Neighbourhood Collective Efficacy Scale (90, 91)		×	×	×	×	×	×
Cost-effectiveness							
Quality of Life Measures (92, 93)		×	×	×	×	×	×
Use of healthcare services		×	×	×	×	×	×
Demographics							
Age, gender, number of children, education level		×					
Marital status, living with family members		×				×	×
Economic activity status, house		×	×	×	×	×	×
Usage of senior citizen center or service		×	×	×	×	×	×
Usage of community/Home care services		×	×	×	×	×	×
Household income in the past month		×	×	×	×	×	×

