### Intervention

#### Structure

The intervention period will last for 6 months, with each intervention component delivered over a standardized two-month period (see Table 2). Participants will be allocated to one of the four study arms:First-arm (individual-level only):

**Table 2 tab2:** Intervention design.

Month	1				2				3				4				5				6			
Week	1	2	3	4	5	6	7	8	9	10	11	12	13	14	15	16	17	18	19	20	21	22	23	24
First-arm	**Individual-level only**																							
	Individual-level (Duration: once a week, 60 min per session, via telephone)								Individual-level maintenance (Duration: once a week, 15 min per session, via telephone)															
Second-arm	**Individual- + interpersonal-level**																							
	Individual-level (Duration: once a week, 60 min per session, via telephone)								Interpersonal-level (Duration: once a week, 60 min per session, via telephone)								Individual- + interpersonal-level maintenance (Duration: once a week, 15 min per session, via telephone)							
Third-arm	**Individual- + interpersonal- + community-level**																							
	Individual-level (Duration: once a week, 60 min per session, via telephone)								Interpersonal-level (Duration: once a week, 60 min per session, via telephone)								Community-level (Duration: once every 2 weeks, 2 h per session, in-person)							
Fourth-arm	**Education-only control group**																							
				X				X				X				X				X				X

X—monthly messages on healthy diet tips, recognizing warning signs of health, understanding dementia, fall prevention tips, health messages, and anti-fraud tips via text, graphics or voice recordings will be sent out.

Participants will receive the individual-level intervention for 2 months, comprising weekly 60-min telephone sessions. This is followed by 4 months of weekly 15-min maintenance sessions delivered via the telephone to reinforce key skills and ensure consistency in intervention duration across arms.Second-arm (individual- + interpersonal-level):

Participants will receive the individual-level intervention in the first 2 months followed by the interpersonal-level intervention in the next 2 months, each delivered as weekly 60-min telephone sessions. In the remaining 2 months, participants will receive weekly 15-min maintenance sessions delivered through telephone to consolidate learning from both components.Third-arm (individual- + interpersonal- + community-level):

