For the focus group discussions, all recordings will be transcribed verbatim by a research assistant. Two independent researchers will then conduct a thematic analysis of the transcripts using NVivo version 15 (95). The research team will review and agree on the identified codes, organizing them into main categories and subcategories. These categories may be condensed and reorganized as needed. The team will ensure consistency, reach consensus on the meaning and structure of the categories, and develop a finalized list. Ultimately, a set of categorized themes with supporting verbatim quotes will be produced to highlight the major strengths and limitations of the interventions and to inform improvements for their future implementation.

To evaluate the cost-effectiveness of the multi-level intervention compared to the control group, a trial-based economic evaluation will be conducted. Health outcomes will be measured as quality-adjusted life years (QALYs), calculated using the standard area-under-the-curve method based on individual EQ-5D-5L responses over the study period. Resource utilization will be estimated from the provider’s perspective, and costs for the intervention, outpatient care, emergency department visits, and inpatient care will be calculated using a bottom-up costing approach. The multi-level intervention will be considered dominant if it achieves higher QALYs at a lower cost than the control group. If it results in higher QALYs but also higher costs, the incremental cost-effectiveness ratio (ICER), defined as the difference in cost divided by the difference in QALYs (ΔCost/ΔQALYs), will be calculated. The intervention will be deemed cost-effective if it is dominant or if the ICER falls below the accepted willingness-to-pay threshold. The probability of the intervention to be accepted as cost-effective will be evaluated by probabilistic sensitivity analysis over the uncertainties of all parameters of costs and QALYs as well as variation of willingness-to-pay threshold from zero to 3× gross domestic product per capita in Hong Kong, presented as acceptability curves.

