Despite these strengths, the study presents several potential challenges. First, participants in the more intensive arms (i.e., individual- + interpersonal-level; and individual- + interpersonal- + community-level) may experience adherence difficulties or intervention fatigue. To mitigate these issues, flexible scheduling will be offered to accommodate participants’ energy levels, health conditions, and personal circumstances. Intervention intensity will also be adjusted to individual needs without compromising the core therapeutic components. For example, volunteers may devote additional time to selected topics, provide tailored feedback or supplementary materials in coordination with the project team, and employ a variety of engagement techniques to support diverse learning styles. A second limitation concerns the risk of participant attrition, particularly given the extended 24-month follow-up period. To address this, monthly check-ins and milestone-based financial incentives will be provided after the intervention period to encourage continued participation, maintain rapport, and reduce dropout rates.

Overall, this study is expected to generate rigorous evidence regarding the effectiveness of multilevel interventions to reduce loneliness among older adults, especially those living with poverty and intersecting social vulnerabilities. By integrating individual, interpersonal, and community components—and leveraging social capital through trained volunteers and technology-supported communication—the intervention is designed to be effective, accessible, affordable, and scalable. The longitudinal design enables the examination of both short- and long-term outcomes, offering insights into sustainable best practices. The findings are anticipated to guide policymakers, practitioners, and community organizations in developing programmes that strengthen social connectedness, improve quality of life, and promote healthy aging at a population level.

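### Healthcare use is recalled over 3 months and capped at three contacts, so 18 of 30 post-baseline months are never asked about and higher counts cannot be recovered for costing

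*Protocol article*

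**What the plan says.** The Cost-effectiveness part of the Measures section describes a self-designed scale. It covers outpatient, emergency and "inpatient medical treatment over the past 3 months at both public and private facilities". On scoring it says: "Frequencies will be rated on a scale from 0 = none to 3 = three times or more".

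In Table 1 the row "Use of healthcare services" is marked at all six assessments. The Measures section places the early ones at "2 months (T1), 4 months (T2), and 6 months (T3) from baseline" and the late ones "at 12 months (T4) and 24 months (T5) after the completion of the intervention". The Structure section says "The intervention period will last for 6 months".

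Under Planned statistical analysis, QALYs are an area under the curve of the EQ-5D-5L responses across the study, and "costs for the intervention, outpatient care, emergency department visits, and inpatient care will be calculated using a bottom-up costing approach". The article names no second source of utilisation data and no rule for turning 3-month reports into a total.

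**The concern.** A bottom-up cost multiplies counts of resource use by unit costs. The item falls short of this in two ways.

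- **Recall and spacing.** The recall is a fixed 3 months, while the visits are 2 months apart during the intervention and 12 months apart afterwards. Early windows overlap, and the late ones leave long gaps.
- **Cap.** The top category is open. A participant whose outpatient visits fall from six to three per quarter scores 3 both times, so a real saving does not register.

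The cost side of Objective 6 (cost-effectiveness) is at stake, and to a lesser degree the precision of the utilisation measure in Objective 5. Much of this is fixed once the form is in use, because an analysis plan cannot restore counts that were never recorded.

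**Working it through.** **Inputs.** Recall is 3 months and the top code is 3 (Measures, Cost-effectiveness). T1-T3 are at months 2, 4 and 6 from baseline, and T4 and T5 are 12 and 24 months after completion (Measures). The intervention lasts 6 months (Structure). Hence T4 = 6 + 12 = month 18 and T5 = 6 + 24 = month 30. The article gives no coverage figure to reproduce.

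**Coverage.** A visit at month t covers [t - 3, t].

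| Visit | Month | Window | Months asked about for the first time, after baseline |
|---|---|---|---|
| T1 | 2 | -1 to 2 | 2 |
| T2 | 4 | 1 to 4 | 2 |
| T3 | 6 | 3 to 6 | 2 |
| T4 | 18 | 15 to 18 | 3 |
| T5 | 30 | 27 to 30 | 3 |

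- Covered: 2 + 2 + 2 + 3 + 3 = 12 of 30 months (40%).
- Never asked about: months 6-15 and 18-27, so 9 + 9 = 18 of 30 months (60%).
- Asked about twice: months 1-2 and 3-4, so 2 months.
- Before baseline: 1 month of the T1 window, which the baseline item also covers.
- Check: 5 windows × 3 = 15 = 12 + 2 + 1.

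**Other reading of the timing.** The Discussion lists 12- and 24-month follow-ups without stating the origin. If T4 and T5 were at months 12 and 24 from baseline, their windows would be 9-12 and 21-24. Months 6-9 and 12-21 would then be unasked, which is 3 + 9 = 12 of 24 months (50%). The 2 duplicated months remain.

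**Cap.** The recorded mean is E[min(X, 3)] = P(X≥1) + P(X≥2) + P(X≥3). The share lost is 1 - E[min(X, 3)] / E[X]. The means and distributions below are assumptions, because the article gives no use rates.

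| True mean per 3 months | Poisson: recorded mean (share lost) | Negative binomial, size 1: recorded mean (share lost) |
|---|---|---|
| 1 | 0.977 (2.3%) | 1/2 + 1/4 + 1/8 = 0.875 (12.5%) |
| 2 | 1.782 (10.9%) | 2/3 + 4/9 + 8/27 = 1.407 (29.6%) |

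At a mean of 0.5 the Poisson loss is 0.4%. With stronger overdispersion (size 0.5) the losses at means 1 and 2 are 21.3% and 40.3%. The direction is certain, because a cap can only lower a count. The size is not. It is probably small for admissions and larger for outpatient visits.

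**Effect of matching the recall to the interval.** Asking about use since the previous visit gives 2 + 2 + 2 + 12 + 12 = 30 of 30 months with no overlap, or 2 + 2 + 2 + 6 + 12 = 24 of 24 on the other reading.

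**The case against.** A reader might infer several stronger things that the article does not support.

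- **That costs will be double-counted in months 1-2 and 3-4 and omitted in the gaps.** The article does not say that raw window totals are summed. Each report could be treated as a quarterly rate and scaled to its interval, and that rule commonly sits in an economic analysis plan. What stands is that scaling replaces observation with an assumption for 18 months: that unobserved months resemble the sampled quarters.
- **That costs and QALYs cover different time.** EQ-5D-5L is collected at the same six visits, and the area-under-the-curve method also interpolates across the long gaps. What stands is narrower: contacts that fall in the gaps are inferred and never asked about.
- **That Objective 5 cannot be answered.** The same 3-month measure, taken in all arms at T4 and T5, still supports a comparison between arms. The cap makes it coarser.
- **That nothing can be repaired once collection starts.** All 18 unasked months lie after T3, so later questions could still be changed. Only capped values already recorded are lost for good.
- **That heavy users are removed.** They stay in the data, recorded as 3. If public and private care are separate items, the effective cap is also higher.
- **That length of stay is not collected.** The form is not shown, and the article condenses it to a few sentences. Absence there does not prove absence on the form, and a unit cost per admission is another possibility.

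The cap itself survives all of this. It is stated outright, it conflicts with the need for counts in bottom-up costing, and no later analysis can reverse it.

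**Conclusion.** The point holds as a mismatch between the instrument and the costing it feeds. On the timing in the Measures section, 18 of 30 post-baseline months (60%) are never asked about, 2 are asked about twice, and 1 pre-baseline month enters through T1. If the late visits are counted from baseline, 12 of 24 months are unasked. The cap understates use by an amount that depends on unknown rates: about 2-11% (Poisson) or 12-30% (negative binomial, size 1) at assumed means of 1 to 2 contacts per 3 months.

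The coverage figures assume that visits occur on schedule and that the stated recall applies at every visit. They describe what is asked, not how the sponsor will compute costs. The primary outcome, the randomisation and the effectiveness analyses of loneliness are unaffected. It should be fixed, preferably before baseline, but it does not threaten the trial's main conclusion.

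**What to change.** 1. **Before T0:** record the actual number of contacts for each type of care in place of the capped category. Add inpatient nights if the form does not already collect them.
2. **T1-T3:** ask about use since the last interview, which removes the overlap and the pre-baseline month.
3. **T4 and T5:** ask about emergency visits, admissions and nights over the whole interval since the previous visit (12 months on the Measures timing). Outpatient visits can keep a shorter recall if the scaling to the interval is stated.
4. **Alternative for the gaps:** the Discussion says that "monthly check-ins and milestone-based financial incentives will be provided after the intervention period". These contacts could carry the questions, but they are described only as a retention measure, and nothing says that blinded interviewers make them. Use them only if blinded staff ask the same questions in the same way in all arms.
5. **Text:** reconcile the T4/T5 timing between Measures and Discussion, and state one common horizon for costs and QALYs.

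The cost is a slightly longer form and more recall error over 12 months. Because windows would then differ in length, utilisation should be compared over time as a rate per month. The arms, sample size and visit schedule do not change.
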